## Abstract

**Rationale:**

Functional strength training in addition to conventional physical therapy could enhance upper limb recovery early after stroke more than movement performance therapy plus conventional physical therapy.

**Aims:**

To determine (a) the relative clinical efficacy of conventional physical therapy combined with functional strength training and conventional physical therapy combined with movement performance therapy for upper limb recovery; (b) the neural correlates of response to conventional physical therapy combined with functional strength training and conventional physical therapy combined with movement performance therapy; (c) whether any one or combination of baseline measures predict motor improvement in response to conventional physical therapy combined with functional strength training or conventional physical therapy combined with movement performance therapy.

**Design:**

Randomized, controlled, observer-blind trial.

**Study:**

The sample will consist of 288 participants with upper limb paresis resulting from a stroke that occurred within the previous 60 days. All will be allocated to conventional physical therapy combined with functional strength training or conventional physical therapy combined with movement performance therapy. Functional strength training and movement performance therapy will be undertaken for up to 1·5 h/day, five-days/week for six-weeks.

**Outcomes and Analysis:**

Measurements will be undertaken before randomization, six-weeks thereafter, and six-months after stroke. Primary efficacy outcome will be the Action Research Arm Test. Explanatory measurements will include voxel-wise estimates of brain activity during hand movement, brain white matter integrity (fractional anisotropy), and brain–muscle connectivity (e.g. latency of motor evoked potentials). The primary clinical efficacy analysis will compare treatment groups using a multilevel normal linear model adjusting for stratification variables and for which therapist administered the treatment. Effect of conventional physical therapy combined with functional strength training versus conventional physical therapy combined with movement performance therapy will be summarized using the adjusted mean difference and 95% confidence interval. To identify the neural correlates of improvement in both groups, we will investigate associations between change from baseline in clinical outcomes and each explanatory measure. To identify baseline measurements that independently predict motor improvement, we will develop a multiple regression model.

## Introduction

This trial addresses an important focus for stroke rehabilitation: the ability of stroke survivors to recover the use of their arm and hand for everyday functional tasks such as picking up a cup, unscrewing a coffee jar lid, and doing up buttons and zippers. Limitations in performing such everyday tasks seriously affect capacity for independent living. At six-months after stroke, only 38% of people who receive rehabilitation have recovered some dexterity 1.

Systematic reviews [for example 2] indicate that repetitive functional task-specific activity can enhance motor recovery. Two training modalities that have attracted considerable attention are constraint-induced movement therapy (CIMT), which consists of repetitive practice of functional tasks combined with constraint of the ipsilesional upper limb, and robot-assisted therapy (RAT), which provides repetitive practice of movements that are required for upper limb functional activity. CIMT is effective between three- and nine-months after stroke 3 but less so when given early after stroke 4. Furthermore, CIMT is suitable only where at least 10 degrees of active movement are present in the paretic thumb and two or more paretic fingers 5. This requirement for a high level of function excludes many stroke survivors 6. RAT has been used in a wider group of stroke survivors but has also been found to be no more effective than an equal dose of conventional therapy 7. Thus, the question of whether a novel treatment aimed at enhancing upper limb functional task-specific activity might be better than routine conventional physical therapy (CPT) remains unanswered.

Functional strength training (FST) combines functional task-specific exercise and strength training, the latter of which is included because the largest impact on upper limb functional recovery after stroke may result from loss of muscle strength 8. Importantly, preliminary data indicate FST may be more effective than another therapy, movement performance therapy (MPT), at equal intensity 9. Both FST and MPT are used in routine CPT.

Evaluation of FST through properly designed clinical trials is crucial. We are aware, however, that a potentially serious barrier to the development of any novel treatment for poststroke motor impairment arises from poor understanding of its mechanisms of action and, in particular, whether it is likely to work in all stroke sub-groups 10. The CIMT and RAT trials recruited patients based on clinical phenotype, but in order to target therapy to those most likely to benefit, this may not be sufficient. It is increasingly recognized that large rehabilitation trials need to include more sophisticated measures of residual brain structure and function in order for researchers to understand the mechanisms of action of treatment and the characteristics of ‘responsive’ patients 10,11. For example, both the pretreatment level of brain activity in primary motor cortex during the performance of a motor task 12 and the degree of damage to descending motor white matter pathways 13 were associated with greater clinical improvement in 24 chronic stroke patients undergoing two-weeks of robot-based therapy. These studies are encouraging, but if we are to incorporate such data into models that can accurately predict therapeutic response, larger sample sizes are clearly required.

Specific objectives of this trial are the following:
to determine whether CPT + FST commenced early after stroke produces greater improvements in upper limb motor recovery than CPT + MPT;to identify similarities and differences in the neural correlates of clinical improvement in response to (a) CPT + FST and (b) CPT + MPT;to determine whether any pretreatment parameters or combinations are sufficiently predictive of improvement in upper limb motor function in response to intervention to enable physical therapy to be targeted at those most likely to respond;to provide estimates of the preliminary cost-effectiveness of CPT + FST and inform the design of a subsequent pragmatic trial.

## Methods

### Design

The trial will be a randomized, controlled, observer-blind trial (Fig. 1).

**Figure 1 fig01:**
[figure not shown]
Flow diagram to illustrate trial design.

### Study population

Study criteria (combined inclusion and exclusion) are as follows:
aged 18 + years;infarction in anterior cerebral circulation territory within the previous 60 days, confirmed by clinical neuroimaging;score at least 11/33 for Motricity Index pinch section 14 but unable to complete the nine-hole peg test (9HPT) 14 in 50 s or less;no obvious spatial neglect as defined by a score of 0 or 1 on Extinction and Inattention sub-scale of the NIH Stroke Scale;no obvious motor dyspraxia or communication deficits as assessed by ability to imitate action with the nonparetic upper limb, as in previous pilot work 15;able, prior to the index stroke, to use the paretic upper limb to lift a cup and drink from it.

### Randomization

The randomization sequence, generated in advance, will stratify participants by clinical center, time after stroke (up to 30 days and 31–60 days), and ability to use the paretic upper limb as assessed by the 9HPT 14 (substantial impairment = able to move one peg or less in 50 s; moderate impairment = able to move two or more pegs in 50 s). An independent telephone randomization service will maintain allocation concealment from the research team prior to randomization. An independent statistician at the Robertson Centre will generate the randomization sequence and will not be involved in developing the statistical analysis plan or programming the trial statistical analysis.

### Interventions

The intervention phase will last for six-weeks. All participants will receive routine CPT provided by the clinical physiotherapists, as in previous pilot work 9. Training will be provided for them to record content and amount of therapy provided daily for home participants, outpatients, and inpatients.

In each clinical center, the extra therapy will be provided by a research therapist responsible for either extra MPT (control) or extra FST (experimental). We will not tell clinical staff which research therapist is responsible for which treatment. This strategy is expected to minimize the potential for therapist bias, although allocation to different forms of exercise-based therapy is more difficult to conceal than, for example, an active or placebo drug, because of observable differences.

Participants in both groups will take part in extra therapy, as prescribed and overseen by a research therapist through direct and nondirect contact, for up to 1·5 h a day, five-days a week for six-weeks. The research therapists will be trained to direct either FST or MPT in accordance with a standardized manual before the trial begins. Fidelity to the manuals will be assessed at the beginning and at regular points throughout the trial with little prior warning to therapists.

### Control intervention (CPT + MPT)

MPT is the component of CPT which emphasizes movement quality rather than quantity. It is based on neurophysiological approaches for which there is evidence that they produce no effect compared with no treatment or a placebo 16. MPT involves joint and soft tissue mobilization, sensory stimulation, facilitation of muscle activity/movement, positioning, retraining normal patterns of movement, and education for the patient/carer. Emphasis is given to hands-on interventions provided by a therapist facilitating and guiding movement (therapist-dependent) to provide sensory input and to optimize postural control and joint alignment in preparation for voluntary movement. Some repetitive practice of functional tasks is included, but without systematic progression in resistance to movement.

Feedback and instructions during MPT encourage an internal focus of attention on the movement performance, for example, amount and direction of elbow movement when lifting a teapot.

### Experimental intervention (CPT + FST)

FST involves repetitive progressive resistive exercise during goal-directed functional activity, with the therapist providing verbal prompting and feedback (therapist-independent). FST is based on the key elements of normal upper limb function (i.e., positioning the hand and then using it to manipulate objects) and is therapist-independent while maintaining participant safety. The focus is on improving the power of shoulder/elbow muscles to enable appropriate placing of the hand, improving production of appropriate force in arm and hand muscles to achieve a specific grasp, and specific resistive functional practice for wrist and finger muscles to maximize ability to manipulate objects. The initial level of load/resistance is the maximum load that still permits five repetitions of action through the available range of muscle length. Treatment is progressed systematically using repetition and increased resistance to movement by changing the limb’s relationship to gravity, changing the amount of friction to overcome, and increasing the size and weight of items (e.g., following an empty cup with a cup containing an increased volume of water). FST involves specific movements for muscle groups, upper limb gross movement patterns underlying functional activity, hand reaching/retrieval activities, hand grip activities, hand manipulation involving entire everyday movements, and using objects such as screw-top canisters, pegs, mugs, and pens. These movements are extended into more complex everyday activities such as placing different food items into a shopping bag, then lifting the bag onto a shelf; tightening/loosening nuts/bolts; opening a bottle and drinking from it; and pouring tea from a pot.

Feedback and instructions encourage an external focus of attention on the effects of movements, for example, whether the teapot has been lifted clearly off the table.

### Outcomes

In accordance with the intention-to-treat principle, every effort will be made to include all randomized participants at outcome and follow-up whether or not they discontinue randomized treatment before the end of the intervention phase. Measurements will be made and processed by assessors blinded to treatment allocation. To assess whether blinding was achieved, we will ask assessors, at outcome and follow-up points, to guess participants’ group allocation. Agreement with actual allocation will be assessed with Cohen’s kappa.

**Clinical efficacy measures** will be made pre-randomization (baseline), the day (± 7) after the six-week intervention phase ends (outcome), and six calendar months (± 14 days) after the index stroke (follow-up).

The primary outcome measure will be the score on the Action Research Arm Test (ARAT) 17, a measure of the primary focus of both interventions – improved upper limb function.

Secondary outcome measures will be (a) Wolf Motor Function Test (WMFT) score 18, (b) hand grip force, and (c) pinch grip force. The upper limb positions for both pinch grip force and hand grip force will be standardized and the myometer set to zero after the participant’s hand/digits are positioned around the bars, ‘at rest’. The instruction given will be ‘squeeze as hard as you can’. Force values will be obtained over three trials, with the greatest value obtained used for data analysis.

**Explanatory measures** will be made at baseline and outcome. Full training will be given to all trial center teams, with comprehensive monitoring and supervision arrangements. Data from all sites will be subject to prompt, rigorous quality control prior to statistical processing. All participants will be provided with full explanations and opportunities to ask questions, plenty of time to be made comfortable, and plenty of time to practice the tasks.

Structural brain imaging will be conducted in all patients in the same location during the same session.

First, a *T*_1_-weighted, 1 × 1 × 1-mm whole-brain image will be obtained using structural magnetic resonance imaging (MRI). Automated normalization, segmentation, and lesion identification will be performed as previously described 19, using spm12 (http://www.fil.ion.ucl.ac.uk/spm/software/spm12). This approach has a high sensitivity for delineating brain lesions and identifying tissue classes, thereby being useful in atrophy and white matter disease. Outputs include normalized lesion maps as well as gray and white matter maps consisting of voxel-wise values representing gray or white matter density.

Second, a map of the static magnetic field will be generated to allow for offline correction of image distortions.

Third, diffusion tensor imaging (DTI) data will be acquired at 2 × 2 × 2 mm. A diffusion tensor model will be fitted to data at each voxel to allow for maps of diffusion parameters (fractional anisotropy, mean diffusivity, and eigenvalues) to be generated for each participant at each scanning session. Probabilistic tractography (http://www.fmrib.ox.ac.uk/fsl) will be used to generate pathways of interest across the group 19, in particular the corticospinal tract.

Fourth, dual-echo *T*_2_-weighted and proton-density whole-brain MRI scans will be acquired at 1 × 1 × 3 mm resolution to allow for accurate delimitation of stroke volumes and for detection of other pathological changes, such as white matter hyperintensities.

A key purpose of FST is to improve the production of appropriate force in different muscles to enhance grasping and manipulation of objects by the paretic hand. We will therefore use a grip force task for functional MRI (fMRI), which is able to detect changes in brain activity corresponding to a force as low as 0.01N. As all participants will be able to produce the beginnings of prehension, they will be able to perform the fMRI grip task. Participants will be scanned while performing isometric handgrips of between 20% and 50% of paretic hand maximum grip force as measured just prior to scanning. Participants will be trained in how to perform the task prior to scanning. The experiment will be conducted according to an event-related design (auditory cues given at interstimulus interval of 7 ± 2 seconds) with actual exerted force recorded 20.

Analysis of fMRI data will follow standard approaches using spm12. Single-participant results will include voxel-wise values for (a) magnitude of brain activity during handgrips and (b) how much brain activity is modulated by handgrip force (20%, 50%). These values are independent of one another and provide complementary information on how the brain is working to generate motor output. In addition, we will use dynamic causal modeling (DCM) 21 to measure (a) connectivity between brain regions (coupling parameters) during grip and (b) changes in connectivity between brain regions (bilinear parameters) with increasing grip force.

Single pulses of transcranial magnetic stimulation (TMS), using a standard figure-of-eight coil, will be given over the hand and arm areas of the primary motor cortex of the lesioned hemisphere and, when possible, the nonlesioned hemisphere. Electromyographic recordings of motor evoked potentials (MEPs) over both contralateral and ipsilateral extensor carpi radialis and biceps brachii muscles will allow for characterization of recruitment curves, which will be constructed by measuring the amplitude of the MEP at between 100% and 130% (where possible) of active motor threshold 20,22.

#### Economic evaluation

Costs and effects will be monitored at baseline and outcome in order to inform the design of a future Phase III study. A preliminary estimate of cost-effectiveness will also be made. Resource items to be monitored will include input by the research therapist, length of stay in the original admission and any subsequent readmission, and other health-care and non-health-care contacts. Levels of informal care will also be monitored. The EuroQoL-5D 23 will be the main measure of effect, as it can be used to estimate the quality-adjusted life year gain.

### Assessment of safety

Comprehensive details of the trial safety monitoring process can be found in the operational trial protocol (http://www.fastindicate.com). In addition to events that may be expected to occur in a trial of this type, pain and fatigue will be particularly monitored, as there is a possibility that either MPT or FST, carried out in addition to CPT, could be associated with overuse syndrome, expressed by experience of pain or fatigue. We will follow the Norwich Clinical Trials Unit system of documenting and reporting serious adverse events (http://www.nnuh.nhs.uk/Dept.asp?ID=681). Adverse events will be recorded from randomization to end of trial.

### Data monitoring body

Ethical approval has been provided by the National Research Ethics Service. The University of East Anglia is the trial sponsor. All necessary local R&D governance approval will be obtained for each center in advance of recruitment. This trial is registered with Current Controlled Trials (ISRCTN19090862) and the UK Clinical Research Network Study Portfolio (UKCRN ID 12967). Independent trial oversight will be provided by a trial steering committee and a data monitoring and ethics committee set up in adherence to the UK Medical Research Council Guidelines for Good Clinical Practice in Clinical Trials.

### Sample size

The clustered data structure (patients grouped according to therapist within each treatment group) is accounted for in the design and analysis 24. This sample size calculation is based on actual ARAT data from our previous early-phase trial 9. Assuming an intraclass correlation coefficient of 0·01 in both treatment arms and three centers with a separate therapist for each randomized arm, a sample size of 99 participants per group would have 80% power to detect a clinically important mean difference of 6·2 in ARAT change when data were analyzed using a two-sample *t*-test with Satterthwaite correction, applying a 5% two-sided significance level and allowing for potentially different standard deviations in the CPT + MPT (7·9) and CPT + FST (19·3) groups. To account for clustering in the design (participants grouped according to therapist within each randomized treatment at each study site), a sample size inflation factor, 1 + (*m*-1)*ICC, is applied, where *m* is the cluster size and ICC is the intraclass correlation coefficient. Assuming that recruitment is evenly distributed across therapists, sample size is therefore inflated to 129 evaluable participants per group. The corresponding mean differences in ARAT change that would be detectable in a study of this size for ICCs of 0·02 and 0·03 would be 7·0 and 7·8 respectively, showing that the design is fairly insensitive to assumptions about the ICC. Finally, to allow for an attrition rate of 10% [7% in our previous single-center trial 9], 144 participants per group will be recruited for a total sample size of 288.

For the explanatory measurements, our experience indicates that of those meeting the criteria for this proposed trial, at least 70% will consent to participate, and 90% of these will complete the measurements. Thus, we anticipate 181 sets of explanatory measurements.

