### Clinical efficacy

Continuous outcome variables will be compared between treatment groups using a multilevel normal linear model. Change from baseline to outcomes (day 43; Fig. 1) will be modeled, adjusting for baseline value, time after stroke, and 9HPT score as patient-level covariates. Which therapist administered the treatment will be included in the model as a zero-mean random effect. We will test, by comparing the log-likelihood, whether a separate random-effect variance is required for therapists delivering each treatment arm or whether a pooled variance is sufficient. The treatment effect will be summarized using the adjusted mean difference and 95% confidence interval.

Secondary analyses will include sensitivity to incomplete follow-up, descriptive analysis at each time-point, statistical modeling of follow-up measures at six-months, and a per-protocol analysis. For safety analysis, the number and percentage of participants experiencing each prespecified category of adverse event will be summarized by treatment group.

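### The stated 80% power uses patient-level degrees of freedom although the treatment contrast rests on six therapists; on the plan's own inputs it is about 57–61% with small-sample degrees of freedom

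*Protocol article*

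**What the plan says.** All references are to the protocol article.

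- **Structure.** The Sample size section assumes "three centers with a separate therapist for each randomized arm, a sample size of 99 participants per group would have 80% power". Under Interventions, each research therapist delivers one of the two extra therapies only. Therapists are therefore nested in treatment, three per arm and six in all.
- **Power calculation.** The target is a "clinically important mean difference of 6·2 in ARAT change", with "potentially different standard deviations in the CPT + MPT (7·9) and CPT + FST (19·3) groups". The test is a two-sample t-"test with Satterthwaite correction", "applying a 5% two-sided significance level".
- **Clustering.** "Assuming an intraclass correlation coefficient of 0·01 in both treatment arms", the number is multiplied by 1 + (m−1)×ICC, giving 129 evaluable per group and, after 10% attrition, 144 per group. The section gives detectable differences of 7.0 and 7.8 at ICCs of 0.02 and 0.03, and from these concludes that the ICC assumption matters little.
- **Analysis.** The Clinical efficacy section models change in ARAT with patient-level covariates and adds: "Which therapist administered the treatment will be included in the model as a zero-mean random effect". It also plans a log-likelihood comparison to choose between one therapist variance and a separate one per arm.

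**The concern.** When whole therapists belong to one arm and therapist is a random effect, the treatment difference is judged against variation between therapists. With three per arm there are 2×(3−1) = 4 degrees of freedom for that variation, however many patients each therapist treats. The inflation factor corrects the size of the standard error. It does not correct for how poorly that standard error is estimated from six therapists. With 4 degrees of freedom the two-sided 5% critical value is 2.78 rather than 1.98.

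At stake is how the result is read. The section describes a 20% risk of missing a difference that it calls clinically important. If the real risk is about 40% or more, a null result would be given more weight than it deserves.

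**Working it through.** **Inputs (Sample size section).** SDs 7.9 and 19.3; difference 6.2; two-sided 5%; ICC 0.01, 0.02 and 0.03; 129 evaluable per group; three therapists per arm, so m = 129/3 = 43.

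**Step 1: reproduce the plan.** Sum of variances: 7.9² + 19.3² = 434.9. Inflation at ICC 0.01: 1 + 42×0.01 = 1.42. SE = √(434.9×1.42/129) = 2.19. Noncentrality = 6.2/2.19 = 2.83. The effective number per group is 129/1.42 = 90.8, for which the Welch–Satterthwaite formula gives about 119 degrees of freedom and 80.3% power. Solving for 80% power gives detectable differences of 6.18, 7.05 and 7.83 at the three ICCs. These match the stated 80%, 6.2, 7.0 and 7.8, and 129/0.9 rounds up to 144.

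The match shows that the Satterthwaite correction deals with unequal patient SDs and does not reach the therapist level.

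(A side point: the intermediate figure of 99 per group does not reproduce. It gives about 84% power; 91 gives 80.3%, and 91×1.42 = 129.2. The totals of 129 and 288 follow from 91, so this does not affect what follows.)

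**Step 2: same standard errors, 4 degrees of freedom (noncentral t).**

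| ICC | Inflation | SE | Power for 6.2, patient-level df | Power for 6.2, 4 df | Difference detectable with 80% power, 4 df | Stated |
|---|---|---|---|---|---|---|
| 0.01 | 1.42 | 2.19 | 80% | 57% | 8.2 | 6.2 |
| 0.02 | 1.84 | 2.49 | 69% | 47% | 9.4 | 7.0 |
| 0.03 | 2.26 | 2.76 | 60% | 40% | 10.4 | 7.8 |

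On 4 degrees of freedom, 80% power needs a difference of 3.76 standard errors; for example, 3.76×2.19 = 8.2.

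**Step 3: separate arm variances.** A Welch test on three therapist means per arm has (7.9²+19.3²)²/[(7.9⁴+19.3⁴)/2] = 2.65 degrees of freedom. Power at ICC 0.01 is then about 45%.

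**Step 4: simulation (300,000 trials per scenario, balanced, no covariates, ICC 0.01).** The ranges cover equal and unequal SDs.

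- t-test on therapist means, 4 df: power 57.4–59.6%. The upper figure, with unequal SDs, comes with a type I error of 6.8%.
- REML, with 4 df when the therapist variance is estimated above zero and patient-level df otherwise: power 58.8–60.6%, type I error 4.4–5.0%.
- REML with a normal (Wald) reference: power about 77%, type I error 6.4–6.7%. The type I error rises to 8.1–8.7% at ICC 0.02 and 9.3–10.2% at 0.03.

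None of these methods gives 80% power at a true 5% level.

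**The case against.** **The plan does deal with clustering.** It does so for the variance, openly, and its figures reproduce under the method stated. That stands. What is left out is the effect of having only six therapists.

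**The inference method may be in an SAP that is not shown.** This is right, and it limits the point. A reader might infer that the trial will run with an inflated type I error. The article does not support that: it names neither a Wald test nor a method for the degrees of freedom, and leaving this to the SAP is normal. Even under a Wald test the excess at the planning ICC is modest. The power statement, however, is in this article, and Step 4 shows that none of the methods tried restores it.

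**Baseline adjustment will recover power.** The planning SDs are for change scores and the model adds baseline value, time after stroke and 9HPT score, so some gain is likely. The article gives no correlation. If residual variance fell equally at both levels by 10%, 20% or 30%, power on 4 degrees of freedom at ICC 0.01 would be about 62%, 66% or 72%. Reaching 80% needs about 43% (1 − (6.2/8.23)²). This is why 57–61% must not be read as the power that the design will deliver.

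**Four degrees of freedom is not a fixed property.** At ICC 0.01 the therapist variance is estimated as zero in about 41–47% of simulated trials, and patient-level degrees of freedom may then apply; the upper end of 57–61% allows for this. In the other direction, the Abstract says that the model adjusts for stratification variables, which include center, while Clinical efficacy does not list center. With center as a fixed effect, 6−1−1−2 = 2 degrees of freedom remain, and at the same standard error power would be about 36%. More than six therapists in practice would raise the degrees of freedom, but the Sample size section assumes one per arm per center.

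**Conclusion.** The claim of 80% power at two-sided 5% for 6.2 points does not hold for the planned model. At ICC 0.01, with pooled variance, six therapists and no credit for covariates, power with small-sample degrees of freedom is about 57–61%, and about 45% if arm variances are kept separate. On 4 degrees of freedom it falls to about 47% and 40% at ICC 0.02 and 0.03.

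The statement that the design is fairly insensitive to the ICC does not hold up either. Even with patient-level degrees of freedom, power for 6.2 points falls from 80% to 60% as the ICC goes from 0.01 to 0.03.

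This is an error in the stated power. The documents do not show that the final analysis will be invalid, and they do not support a single replacement figure free of assumptions.

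**What to change.** 1. **Sample size section.** Keep 288 participants. Restate power and detectable differences with therapist-level degrees of freedom, naming the assumptions: ICC, pooled or separate variances, three therapists per arm and no covariate credit. On 4 degrees of freedom the detectable differences are about 8.2, 9.4 and 10.4 points at ICCs of 0.01, 0.02 and 0.03. Show any gain from baseline adjustment as a range, since no correlation is given.
2. **Same section.** Drop or qualify the sentence on insensitivity to the ICC.
3. **Primary analysis, only if the SAP does not already provide for it.** Fit the model by REML and base the p-value and 95% confidence interval on Satterthwaite or Kenward-Roger degrees of freedom. A large-sample Wald interval would carry a type I error of about 6.5% at ICC 0.01 and about 10% at 0.03.

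The cost is a few sentences and a software option. Recruitment and trial conduct do not change. The price is a less favourable power statement and a wider confidence interval.
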